## Methods and design

This study involves a mixed-methods randomized controlled trial of Dignity Therapy versus a Supportive Attention control group (please see Fig. 1 for an overview of the study activities). Specifically, this study involves providing either Dignity Therapy or Supportive Attention to 90 patients receiving hospice or palliative care who have a primary diagnosis of cancer. The aim is to assess whether patients who receive Dignity Therapy will exhibit significantly greater contentment, hope, gratitude, positive affect and sense of closure, and whether patients’ levels of resilience and self-efficacy mediate or moderate this effect.

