**Fig. 1 Fig1:**
[figure not shown]
Study flow-chart of the randomized controlled trial of Dignity Therapy focused on positive outcomes

All of the patients in the study will be followed for 14 days, with evaluations occurring at baseline and at the end of treatment. Each hour-long therapy session also includes the administration of two brief assessments related to positive affect and life satisfaction to explore whether each session provides some level of beneficial effect (please see Table 1 for a list of the study assessments and schedule). This study protocol and all accompanying materials have been approved by the University of California, San Diego Institutional Review Board and Human Research Protections Program.

**Table 1 Tab1:** Study outcomes and assessment schedule for the randomized controlled trial of Dignity Therapy focused on positive outcomes

Instrument	Time in minutes	Baseline	Session 1	Session 2	Session 3	Session 4	Post-Test
Positive and Negative Affect Scale (PANAS)	5	•	•	•	•	•	•
Life Closure Scale (LCS)	10	•					•
Hearth Hope Index (HHI)	5	•					•
Satisfaction with Life (BPFSS)	3	•	•	•	•	•	•
Gratitude Questionnaire (GQ-6)	5	•					•
Connor-Davidson Resilience Scale (CD-RISC)	7	•					•
Hospital Anxiety and Depression Scale (HADS)	5	•					•
Life Evaluation Questionnaire (LEQ)	10	•					•
Self-Efficacy (GSE)	5	•					•
Study Completion Questionnaire	5						•
	TOTAL	70	10	10	10	10	75

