##### Resilience

The Connor-Davidson Resilience Scale (CD-RISC) is comprised of 25 items using a 5-point Likert scale. The CD-RISC measures how people have felt in the past month, and scores range between 0 and 100; higher scores indicating greater resilience. Sample items include: “I tend to bounce back after illness, injury, or other hardships,” and “I give my best effort no matter what the outcome may be.” The items pertain to concepts such as personal competence, a tolerance of negative affect, a positive acceptance of change, and tenacity. This scale is used to identify whether resilience is a mediating or moderating variable among patients in the study [30].

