In order to assess how resilience and self-efficacy may mediate or moderate the impact of Dignity Therapy, we will use a RRM method similar to the primary hypotheses. The effect of mediator and moderator variables will be explored using RRM for each candidate mediator and moderator as a main effect and an interaction [35, 36]. If the interaction effect is significant, pairwise comparisons of groups will be performed. These analyses will examine interactions of treatment group with time at each level of the mediator and moderator, and evaluate treatment levels within each subgroup.

Finally, the time course of treatment of each individual will be modeled by projecting the outcome measures on orthogonal linear, and quadratic of time. Model diagnostics will be used to determine the suitability of an autoregressive error component and nonlinear effects for assessment time. Analyses will be performed using the SPSS (version 21.0) procedures. Data will be included for all patients completing at least one assessment after baseline.

The assumptions for sample size and power calculation are based on our pilot data and using procedures described by Hedeker et al. for Random Regression Models (RRM) [37]. With the proposed sample size of 86 subjects without attrition or 90 subjects adjusted for attrition (45 for each of the two groups), the study will have power of 80 % to yield a statistically significant result for a medium effect size. Here, medium effect size is defined as a between-group difference increasing linearity from 0 at baseline to 0.5 SD units at session 4. Results from this study will provide information regarding appropriate power calculations to further determine necessary effect sizes for larger-scale studies in the future.

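### Mediation is analysed with a moderation procedure, and comparing arms within levels of the mediator either cannot show mediation or is biased

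*Protocol article*

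**What the plan says.** The aim is declared in the protocol article under Methods and design: the study will assess "whether patients’ levels of resilience and self-efficacy mediate or moderate this effect". The Background presents it as a further line of inquiry. The Resilience and Self-efficacy paragraphs each give their scale the job of identifying a mediating or moderating variable.

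Statistical analyses gives one procedure for both roles:

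- Effects are "explored using RRM for each candidate mediator and moderator as a main effect and an interaction".
- Comparisons between pairs of groups follow only when that interaction reaches significance.
- "These analyses will examine interactions of treatment group with time at each level of the mediator and moderator", followed by treatment comparisons inside each subgroup.

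The same paragraph states no treatment-to-mediator step and no indirect effect. It does not say whether the baseline or the post-test score enters the model.

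On timing, the text describes follow-up "with evaluations occurring at baseline and at the end of treatment". Table 1 marks CD-RISC and GSE at those two visits only. The Life Closure Scale has the same two visits, and the PANAS is also taken at all four sessions. The Resilience paragraph adds: "The CD-RISC measures how people have felt in the past month".

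**The concern.** Moderation asks whether the treatment effect differs across values of a patient characteristic. Mediation asks whether treatment changes a variable that in turn changes the outcome. The first is an interaction and the second is a product of two paths. A plan whose follow-up depends on the interaction answers only the first question.

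The within-level comparison adds a second problem. If the levels come from baseline scores, the comparison is protected by randomisation but says nothing about mediation. If they come from post-test scores, patients are grouped by something treatment may have changed, and the arms within a group are no longer comparable. At stake is a declared secondary aim: a mediation statement could rest on an analysis that does not estimate mediation, or a subgroup difference could be produced by the grouping itself.

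**Working it through.** The article gives no figure for this analysis, so there is nothing to reproduce. The check has three parts.

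**1. Does the interaction test detect mediation?** Write T for arm, M for mediator and Y for outcome at post-test:

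- M = a·T + error
- Y = c·T + b·M + error

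The indirect effect is a·b. The T×M coefficient in this model is zero whatever a and b are, so its test rejects at the nominal 5% whether a·b is large or nil. A simulation of this simplified model (not the full random regression) confirms it. It used 86 patients (the article's figure before attrition), 1:1 allocation, two-sided 0.05 and 4,000 runs per row. The path sizes are assumptions.

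| Scenario | Interaction, continuous M | Interaction, median split | Both paths significant |
|---|---|---|---|
| a=0.5, b=0.5, c=0 (full mediation) | 4.8% | 4.7% | 62.7% |
| a=0.8, b=0.6, c=0 (full mediation) | 4.6% | 4.7% | 95.8% |
| a=0, b=0, c=0.5 (no mediation) | 5.0% | 4.7% | 0.2% |

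**2. What does a within-level comparison on post-test scores estimate?** Take a=0.5, unit variance of M within arm, and a split at the pooled median, 0.25. In the upper half the arm means of M are:

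- treated: 0.5 + φ(0.25)/Φ(0.25) = 0.5 + 0.3867/0.5987 = 1.146
- control: φ(0.25)/(1-Φ(0.25)) = 0.3867/0.4013 = 0.964

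The difference is 0.182, and by symmetry it is the same in the lower half.

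- *Full mediation, b=0.5.* The total effect is 0.5 × 0.5 = 0.25 SD and the direct effect is 0. Each half shows 0.5 × 0.182 = 0.09 SD (simulation: 0.09), which is neither.
- *Shared unmeasured cause of M and Y, assumed loading 0.6 on each, no treatment effect on Y.* The total and direct effects are both 0. Each half shows 0.6² × (0.182 - 0.5) = 0.36 × (-0.318) = -0.11 SD (simulation: -0.11), produced entirely by the grouping.
- *Treatment does not move M (a=0, b=0, c=0.5).* Each half shows 0.50 SD, the true value. The distortion appears when treatment changes M, which is the case mediation supposes.

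**3. Which score could be used?** Table 1 leaves two options for each scale.

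| Score | Can moderate | Can mediate | Within-level arm comparison |
|---|---|---|---|
| Baseline | yes | no, it precedes treatment | valid |
| Post-test | no, treatment may affect it | possible in principle | biased, as in part 2 |

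The post-test score is taken at the same visit as the final Life Closure Scale and PANAS, and after the session PANAS scores. It therefore does not precede any outcome measurement.

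**The case against.** The strongest reply has four parts.

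*The main-effect term.* A mediator entered beside treatment estimates the mediator-to-outcome path. Resilience and self-efficacy are also secondary outcomes in the Abstract, so a treatment-to-mediator estimate may exist. The sources cited for the method are not at hand. This stands in part: the pieces could be assembled. The article does not assemble them, and it keys follow-up to the interaction and to subgroups of the mediator.

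*Which visit's score.* A reader might infer that the plan does split on post-test scores. The article does not say so. The bias in part 2 of the working is therefore conditional, but the alternative, a baseline score, cannot mediate.

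*The simulation.* The 5% rate follows by construction because no interaction was built in, and the main-effect term was not judged on its own. Both are true. The table only illustrates that the stated trigger carries no information on a·b.

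*Recall and categories.* A reader might infer that the one-month CD-RISC recall dilutes change by a known share. With an assumed 30-day month, (30-21)/30 = 30% or (30-14)/30 = 53% of the window precedes baseline, depending on whether the article's 3 weeks or its 14 days applies; those two statements need reconciling. That is a share of calendar days. Reading it as dilution assumes that patients weight every day equally, which no text supports, and no recall period is given for GSE. Likewise, the wording on levels and subgroups suggests cutting the scales into groups, but no cut-points are given. Neither should be asserted as fact.

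**Conclusion.** The point holds as a defect in a stated rule for a secondary, exploratory aim. The interaction that triggers follow-up does not distinguish mediation from none. The within-level comparison is uninformative about mediation with baseline scores and biased with post-test scores. Under the assumed paths the bias turns 0.25 SD into about 0.09 SD, or 0 into about -0.11 SD. Those sizes depend on the assumed paths, the assumed loading, a median split and a single post-test outcome; the direction of the argument does not.

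A reader might go further and conclude that the mediation aim cannot be addressed at all, or that a significant interaction will be reported as mediation. The documents do not support either. An indirect effect can be estimated from the planned data, though without time order, and nothing states how an interaction will be reported. Moderation by baseline scores and the primary comparison are untouched.

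**What to change.** 1. **Moderation.** State that only baseline CD-RISC and baseline GSE are used, preferably as continuous terms in the treatment-by-time interaction.
2. **Within-level comparisons.** Remove mediators from the text that examines treatment effects "at each level of the mediator and moderator, and evaluate treatment levels within each subgroup".
3. **Mediation.** Either withdraw the claim, or report (i) the treatment effect on the post-test mediator adjusted for its baseline, (ii) the mediator-to-outcome effect given treatment and both baselines, and (iii) an interval for the indirect effect.
4. **Labelling.** Call the mediation result exploratory. State that mediator and outcome come from the same visit, so neither time order nor absence of confounding is established. Changing the test does not cure this: under the shared-cause scenario in the working, with b=0, the two-path test falsely rejected in about 58% of runs.
5. **Limitation.** Note, without a figure, that the post-test CD-RISC recall period reaches back before baseline.

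The cost is revised wording and a few extra models, with no new data. The price is a weaker mediation claim. Precision will also be limited: with 20% deaths, 90 × 0.80 = 72 patients remain, and the two-path test at a=0.5, b=0.5 then rejects in 54.0% of runs.

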### Statistical analyses

Descriptive statistics will be obtained for all variables, including distributions, means, medians, variances, standard deviations, skewness, kurtosis, ranges, and quartiles. Tests of normality of continuous measures will be made using the Shapiro-Wilk W and the Kolomogorov D statistics in conjunction with plots of the distribution of data and descriptive measurements. The data will also be examined for homogeneity of variance. An appropriate statistical method will be employed to correct for any abnormalities (such as log, square root, and inverse). All statistical tests will be two-tailed. Differences will be considered statistically significant provided a *p*-value ≤ 0.05 is obtained. The comparability of the two treatment groups in baseline demographic and clinical features will be tested with analyses of variance (ANOVAs) for continuous variables and Chi-square analyses for dichotomous variables.

Analyses will be based on a Random Regression Model (RRM) for continuous data using a generalized linear model [33, 34]. This model was selected over more traditional analytic approaches such as a change score, end-point, or repeated measures analysis of variance for several reasons. First, a 14–20 % death rate is anticipated based on pilot studies, and using this statistical method, we will be able to include all of the patients with missing data, early termination, or death without relying on data imputation procedures. Second, both fixed and time-varying covariates and systematic person-specific deviations from the average time trend are allowed in this method. A fully saturated treatment by time model will be utilized for inference. Co-variance structure will be chosen based on Akaikes Information Criterion (AIC). Random group level treatment effects will also be evaluated for importance based on the model AIC. This allows for any group level effects to be incorporated into the model. Denominator degrees of freedom will be calculated using the Kenward-Roger small sample correction.

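### The post-baseline entry rule excludes randomised patients whom the model was chosen to keep, and does not say whether it applies per patient or per outcome

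*Protocol article*

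**What the plan says.** All the statements at issue are in the protocol article, under Statistical analyses.

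- **Reason for the model.** The random regression model is preferred to change-score, end-point and repeated-measures analyses. The first reason given is mortality: a 14–20% "death rate is anticipated based on pilot studies", and with this method "we will be able to include all of the patients with missing data, early termination, or death without relying on data imputation procedures".
- **Analysis set.** In the paragraph that names the software: "Data will be included for all patients completing at least one assessment after baseline".
- **Inference.** A saturated treatment-by-time model. The target is a difference growing from 0 at baseline "to 0.5 SD units at session 4".

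Table 1 gives the schedule. The PANAS and the life-satisfaction item are taken at baseline, at sessions 1 to 4 and at post-test. The LCS, the other primary outcome, is taken at baseline and post-test only.

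**The concern.** A patient who dies or stops before session 1, and so has no later assessment, is kept under the reason given for the model and excluded under the analysis-set rule. The rule makes entry to the analysis depend on survival and retention after randomisation. Session 1 is also the first therapy visit, and only one arm works towards a legacy document, so early loss could differ between arms.

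The rule is unnecessary. A likelihood-based mixed model takes baseline-only patients as they are, and their baseline scores carry information when loss is related to baseline state. Dropping them can bias the treatment-by-time contrast even when the data are missing at random, which is the condition under which the model is otherwise sound.

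The rule is also ambiguous. It does not say whether the required assessment may be on any instrument or must be on the outcome being analysed. For the LCS the two readings give different analysis sets.

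**Working it through.** The plan gives no figure for the number excluded, so there is none to reproduce. The sample sizes of 86 and 90 do not bear on this point.

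**Step 1. Who is excluded**

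| Situation | Rule applied per patient (any instrument) | Rule applied per outcome |
|---|---|---|
| Lost before session 1, nothing later | Out of PANAS and LCS | Out of PANAS and LCS |
| Lost after session 1, no post-test | In for PANAS; baseline LCS kept | In for PANAS; out of LCS |
| Post-test completed | In | In |

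The first row conflicts with the stated reason for the model on either reading. The second row conflicts with it only per outcome.

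**Step 2. Effect of dropping baseline-only patients**

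Inputs from the protocol: 45 per arm and a 0.5 SD target. Assumptions: one follow-up time, unit SD, baseline-to-follow-up correlation r, and baseline treated as a response time with its own mean in each arm.

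Within an arm, let B_all be the baseline mean of all patients, B_obs the baseline mean of those with follow-up, and P_obs their follow-up mean.

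- Keeping everyone, estimated change = P_obs + r(B_all − B_obs) − B_all
- Dropping baseline-only patients, estimated change = P_obs − B_obs
- Dropped minus kept = (1 − r)(B_all − B_obs)

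**Step 3. A few early losses**

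Suppose 4 of 45 patients in one arm are lost before session 1 and their baseline differs by 0.5 SD from that of the other 41. Then B_all − B_obs = 0.5 × 4/45 = 0.044 SD.

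| Assumed r | (1 − r) × 0.044 | Share of 0.5 SD |
|---|---|---|
| 0.4 | 0.027 SD | 5% |
| 0.6 | 0.018 SD | 4% |
| 0.8 | 0.009 SD | 2% |

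**Step 4. Per-outcome reading for the LCS**

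Simulation with 45 per arm and a true effect of 0.5 SD. Loss is about 17–20%. In one arm only, loss is more likely at low baseline (log-odds rising by 1 per SD). Data are missing at random given arm and baseline. The results below are at 20% loss; at 17% the shifts are slightly smaller.

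| Selective loss in | r | Baseline-only kept | Baseline-only dropped |
|---|---|---|---|
| Supportive Attention | 0.5 | 0.50 | 0.59 |
| Supportive Attention | 0.7 | 0.50 | 0.55 |
| Dignity Therapy | 0.5 | 0.50 | 0.41 |
| Dignity Therapy | 0.7 | 0.50 | 0.45 |

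The largest shift is 0.59 − 0.50 = 0.09 SD, or 0.09/0.5 = 18% of the target. It can go in either direction.

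**The case against.** The strongest reply is that the conflict is narrow. The first statement describes what the method is able to do, and patients who die or stop after session 1 are kept for the PANAS, as promised. Only those lost before any later assessment are excluded, and nothing suggests that they are many. This stands as a limit on size. It does not remove the conflict, because the rule gives up part of the benefit for which the model was chosen.

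Several stronger conclusions might be inferred, and the documents do not support them:

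- **That the LCS analysis is completers only.** This follows only if the rule applies per outcome. Read literally, a session 1 PANAS score admits the patient, and the baseline LCS stays in.
- **That the rule costs the LCS every patient who dies.** The anticipated rate would be 0.14 × 90 = 12.6 to 0.20 × 90 = 18 patients, but the protocol gives no time window for it. For those who do die before post-test, no LCS outcome exists under any analysis set. Death causes that loss, not the rule.
- **That the shift in Step 3 is 0.044 SD.** That is the shift in one arm's raw baseline mean. The treatment-by-time contrast moves by only (1 − r) times as much.
- **That a separate analysis for deaths, such as ranking death below all survivors, must be added.** How to handle death is debatable and commonly left to an analysis plan, which is not shown here. With 45 per arm, such a ranking could let chance imbalance in deaths drive the comparison.

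Two further limits stand. If the lost patients differ only in follow-up that was never observed, keeping their baseline scores corrects nothing. And the protocol does not say whether baseline is assessed before allocation; if it is assessed after, requiring a baseline score is itself a post-randomisation condition, though a milder one.

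**Conclusion.** The point holds in limited form. The section gives two incompatible accounts of who is analysed, and the narrower one is a survival- and retention-dependent exclusion that the planned model does not need. Its scope is unclear for one of the two primary outcomes.

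The size is unknown, because the protocol gives neither the number lost before session 1 nor any loss by arm. Under the assumptions shown, the bias is about 0.01 to 0.03 SD for a handful of early losses, and up to about 0.09 SD for the LCS on the per-outcome reading with selective loss in one arm. Both figures assume arm-specific baseline means in the treatment-by-time model and loss that depends on baseline. They are illustrations, not forecasts. The correction is worth making because it is simple and removes an avoidable source of bias.

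**What to change.** Delete the sentence "Data will be included for all patients completing at least one assessment after baseline". In its place, define the analysis set as all randomised patients with a baseline score on the outcome concerned, analysed in the arm to which they were randomised, in the planned mixed model. Baseline-only patients then contribute, the set agrees with the stated reason for the model, and the question of any instrument versus the outcome analysed no longer arises.

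The cost is a change of wording in the analysis section. It needs no new data, no extra visits and no change to the model.

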### Study sample

This study will sample 90 cancer patients receiving hospice or palliative care. These 90 participants will be randomized to either Dignity Therapy (*n* = 45) or Supportive Attention (*n* = 45). Of the 45 patients completing the Dignity Therapy, 25 randomly-selected participants will be asked to complete qualitative interviews regarding their perspectives on the treatment as well as the study’s use of positive outcomes.

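### The attrition allowance behind the sample size (86 raised to 90, or 4.4%) does not fit the 14–20% deaths expected in the same section, so the stated 80% power is probably a few points too high.

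*Protocol article*

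**What the plan says.** All the planning figures are in the protocol article, under Statistical analyses.

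- **Sample size.** "the proposed sample size of 86 subjects without attrition or 90 subjects adjusted for attrition", split 45 and 45.
- **Power.** "the study will have power of 80" per cent "to yield a statistically significant result for a medium effect size". The medium effect is defined as "a between-group difference increasing linearity from 0 at baseline to 0.5 SD units at session 4".
- **Test.** "All statistical tests will be two-tailed", with significance declared when a p-"value ≤ 0.05 is obtained".
- **Expected loss.** In explaining the choice of a random regression model, the section gives a figure of 14–20%: this "death rate is anticipated based on pilot studies". Missing data and early termination are named alongside death. The model is said to keep all such patients without imputation, and anyone with at least one assessment after baseline is analysed.
- **Assessment schedule (Table 1).** The PANAS is given at all six visits. The Life Closure Scale is given at baseline and post-test only. Both are primary outcomes.

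**The concern.** The sample size paragraph allows for losing 4 patients in 90. The analysis paragraph of the same section expects 12.6 to 18 deaths in 90 (90 × 0.14 and 90 × 0.20), and other withdrawals would come on top. Both the power assumptions and the death rate are attributed to pilot work, so they should agree, and nothing in the text links them.

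The power statement is the only justification given for 90 patients. If it is too favourable, a null result would be read as coming from a better powered trial than was run. The section also says the results will inform power calculations for larger studies, so the optimistic allowance could be carried forward.

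**Working it through.** **Inputs from the article.** Two-sided α = 0.05; power 80%; difference rising linearly from 0 to 0.5 SD; 86 patients (43 per arm) with complete data; 90 (45 per arm) enrolled; deaths 14–20%.

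**Assumptions, because the article does not state them.** The within-patient correlation, the number of time points and the timing of losses. For the Life Closure Scale, which is not measured at session 4, the 0.5 SD difference is taken to apply at post-test.

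**1. The plan's own 86.** With z = 1.960 + 0.842 = 2.802, a plain comparison at one time point needs 2 × 2.802² / 0.5² = 62.8, so 63 per arm or 126 in total. That is not 86. A longitudinal calculation can give 43 per arm if the correlation is chosen to fit:

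- Change from baseline to end: 2 × 2.802² × 2(1 − ρ) / 0.25 = 43 gives ρ = 0.66.
- Slope over five visits (baseline to session 4): ρ = 0.57 with compound symmetry, or 0.90 between adjacent visits with AR(1).

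So 86 is attainable but cannot be confirmed. Every power figure below takes it as given.

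**2. The attrition step.** 1 − 86/90 = 4.4%. Also 86 × 1.05 = 90.3 and 86/0.95 = 90.5, so 90 corresponds to roughly 4.4–5% under simple inflation.

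**3. Life Closure Scale.** Power = Φ(2.802 × √(ratio) − 1.960).

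- *Only patients with a post-test count.* 90 × 0.86 = 77.4 and 90 × 0.80 = 72. Then Φ(2.802 × √(77.4/86) − 1.960) = 75.7% and Φ(2.802 × √(72/86) − 1.960) = 72.7%.
- *Baselines of lost patients kept in the model.* With a fraction p reaching post-test, the variance of the change is proportional to (1 − ρ²)/p + (1 − ρ)². With ρ = 0.658 this is 0.685 at p = 1, 0.777 at p = 0.86 and 0.827 at p = 0.80. The total needed for 80% power rises from 86 to 97.6 and 103.8. Power with 90 is 76.7% and 74.2%.

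The timing of losses makes no difference here, since there is no visit between baseline and post-test.

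**4. PANAS.** Slope model over five visits, generalised least squares, calibrated so that 43 per arm gives 80%. Power with 90 enrolled:

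| When losses occur | Compound symmetry, 14% / 20% | AR(1), 14% / 20% |
|---|---|---|
| All straight after baseline | 76.8% / 74.2% | 76.7% / 74.2% |
| Evenly over visits | 77.5% / 75.4% | 78.4% / 76.8% |
| All just before the last visit | 79.0% / 77.7% | 80.2% / 79.6% |

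Using six visits, or testing the contrast between last visit and baseline, moves these a little. Evenly spread loss stays at or below 79%, and last-visit loss with strong serial correlation runs from 79% to 81%. A random-slope model with a large slope variance behaves like the AR(1) case for late loss (80–81%), but falls to about 73% when 20% are lost straight after baseline. In these models 90 patients hold 80% only up to about 5–8% evenly spread loss.

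**5. Effect detectable with 80% power.** Completers only: 0.5 × √(86/77.4) = 0.527 and 0.5 × √(86/72) = 0.546. With partial data and even loss under compound symmetry, 95.8 and 100.8 patients are needed, so 0.5 × √(95.8/90) = 0.516 and 0.5 × √(100.8/90) = 0.529. Overall, about 0.52–0.55 SD.

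**The case against.** The strongest reply is that 4.4% and 14–20% are not the same kind of number. In a random regression model a patient who dies after several visits still contributes, so a 14–20% death rate does not cost 14–20% of the information, and the inflation needed is smaller than 1/(1 − d). The 4.4% is therefore not necessarily the attrition rate the sponsor assumed. This stands for the PANAS, and it has two consequences:

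- A reader might infer that 90 patients simply cannot deliver 80% power. The article does not support that for the PANAS: late losses with a serial correlation near 0.9 leave power at about 80%.
- A reader might infer that 86/0.86 = 100 to 86/0.80 = 107.5 patients are needed. That is the completers-only answer. With losses spread evenly and partial data kept, the requirement is about 93–98 at 14% and 97–104 at 20%.

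The reply does not remove the point. Even with partial data credited, 90 covers only about 5–8% evenly spread loss, and the favourable corner needs both a timing of deaths and a correlation that the article does not claim. For the Life Closure Scale there are no intermediate visits to credit.

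It is also fair to say that a condensed article may leave the correlation out. That omission is not the fault raised here; the fault is two stated figures that do not fit together.

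Finally, the Study sample section's phrase "Of the 45 patients completing the Dignity Therapy" might be read as an assumption of no loss at all. It is loose wording about drawing 25 interviewees. The sentence before it already says that 90 are randomised, and with 14–20% deaths 36 to 39 completers would remain (45 × 0.80 and 45 × 0.86). It has no bearing on power.

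**Conclusion.** The point holds as an inconsistency: an allowance of 4 patients in 90 stands beside 14–20% expected deaths, before other withdrawals. The likely effect is moderate.

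- **Life Closure Scale:** about 73–77% power instead of 80%.
- **PANAS:** about 74–79% under early or evenly spread loss, and about 80% only in the late-loss corner.

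The shortfall from deaths alone is at most about 7 points, and other withdrawals would add to it.

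The inconsistency itself needs no modelling. Confidence in the exact power figures is only moderate, because they depend on accepting an 86 that cannot be reproduced and on correlations solved to match it. This should be corrected, but it does not undermine the design.

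**What to change.** Keep 90 patients. Recompute the power of 90 enrolled under the plan's own 14–20% loss, or give the effect detectable with 80% power (about 0.52–0.55 SD on the assumptions above). Do this separately for the PANAS and the Life Closure Scale, since only the PANAS gains from intermediate visits. State the attrition rate, its timing, the correlation and the number of time points used. The sponsor should take the new figures from its own pilot inputs; those given here show the size of the gap and are not replacement text.

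The cost is one recalculation and a reworded paragraph. The stated power becomes a few points less favourable. No extra patients are needed, and the analysis does not change.
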